### Secondary outcome

A secondary outcome for this trial is the proportion of enrolled infants who require exchange transfusion. FS-PT will be considered at least as efficacious as CPT if the proportion of infants who require exchange transfusion under FS-PT is no more than 5% greater than the proportion under CPT.

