
## Methods/design

### Aims and hypotheses

The primary goal of this study is to demonstrate that the efficacy of FS-PT is no worse than that of CPT, with a non-inferiority margin of 10%. In effect, our null hypothesis is that this margin is above 10% suggesting that FS-PT is inferior to CPT.

The secondary goal of the study is to demonstrate that the proportion of infants who require exchange transfusion under FS-PT is no worse than that under CPT, with a non-inferiority margin of 5% based on a clinical rationale that FS-PT is non-inferior to CPT and still better than no treatment. This was also informed by the results of a meta-analysis of RCTs comparing CPT with no treatment which estimated that 10 infants needed to be treated with CPT to prevent an exchange transfusion
[26].

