#### Evaluation criteria

Change in TSB level per hour of therapy defined as a binary variable. The TSB level will be measured immediately before beginning therapy on a given day and immediately after therapy is completed that day, and the change in bilirubin level in mg/dl per hour of therapy will be calculated. For infants who are less than 72 hours old in the morning, the treatment will be judged efficacious if the bilirubin level rises more slowly than 0.2 mg/dl per hour of therapy that day. For infants who are more than 72 hours old, the treatment will be judged efficacious if the bilirubin level falls. Efficacy will be evaluated only for days in which the treatment was deemed safe (that is, when the infant did not have to be removed from PT due to a need for physician treatment for sunburn or dehydration, persistent temperature instability defined as two or more episodes of temperatures <35.0 or >39.0°C, or failure to return to normothermia (defined as 35.5 to 38.0°C) within 1 hour of being removed from PT). The average efficacy of each type of PT, defined as the proportion of safe days where a given therapy was used in which the therapy was efficacious, will be compared. FS-PT will be considered at least as efficacious as CPT if the average efficacy on days where FS-PT was used is no worse than 10% less than the average efficacy on days where CPT was used.

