### Exit/discontinuation/withdrawal criteria

Subjects will exit the study (will cease to receive FS-PT or CPT) if any of the following conditions occur: 1) persistent temperature instability defined as two or more episodes of temperatures <35.0°C or >39.0°C; 2) failure to return to normothermia (defined as 35.5°C to 38.0°C) within 1 hour of being removed from PT; 3) physician treatment for dehydration or sunburn is required; 4) TSB level reaches exchange transfusion levels; 5) inter-current illness not compatible with PT or needing more care than can be provided in the FS-PT canopy or CPT ward; 6) infants requiring transfer to another hospital; 7) parent request; 8) subject death; 9) subject completes the protocol (TcB or TSB level is no longer elevated); 10) subject’s well-being, in the opinion of the Investigator, would be compromised by study continuation; 11) Institutional Review Board (IRB) recommendation; or 12) subject’s risk level indicates PT should be stopped.

Infants who have been withdrawn from the study will have a physical examination and a final TcB. Safety data will be analyzed for all days in which the subjects spend any time under either FS-PT or CPT.

Efficacy will be evaluated for all days in which the treatment was deemed safe (that is, when the infant did not have to be removed from PT due to a need for physician treatment for sunburn or dehydration, due to persistent temperature instability defined as two or more episodes of temperatures <35.0 or >39.0°C, or due to failure to return to normothermia (defined as 35.5 to 38.0°C) within 1 hour of being removed from PT).

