### Data collection and analysis

Data will be collected on paper case report forms and entered via a web interface into a secure database. The study data will be collected and managed using REDCap (Research Electronic Data Capture) electronic data capture tools hosted at the University of Minnesota’s Academic Health Center. REDCap is a secure, web-based application designed to support data capture for research studies, providing: 1) an intuitive interface for validated data entry; 2) audit trails for tracking data manipulation and export procedures; 3) automated export procedures for seamless data downloads to common statistical packages; and 4) procedures for importing data from external sources.

Demographic data will be summarized and compared between the treatment and control groups using appropriate methods, such as Pearson’s chi-square test for categorical variables and two-sample t-tests for continuous variables. The primary objective is to compare the efficacy of FS-PT and CPT. A 95% exact binomial confidence interval for the true difference in efficacy between the FS-PT treated and CPT control groups will be calculated. FS-PT will be deemed non-inferior to CPT if the calculated confidence interval does not extend more than 10% below the equivalence point.

We plan to conduct three distinct analyses: an intent-to-treat analysis based on the assigned treatment for each enrolled infant, an as-treated analysis based on the actual treatment received on a given day and a per-protocol analysis including only enrolled infants who received the assigned treatment on all of their treatment days.

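### The 5-point non-inferiority claim on exchange transfusion has no confidence limit attached; followed as written, its rule passes a true 5-point excess about half the time

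*Protocol article*

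**What the plan says.** Under Aims and hypotheses, the secondary goal is to show that exchange transfusion under FS-PT is no worse than under CPT, "with a non-inferiority margin of 5% based on a clinical rationale". The supporting figure is a meta-analysis result that "10 infants needed to be treated with CPT to prevent an exchange transfusion".

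The Secondary outcome section turns this into a success criterion: FS-PT counts as at least as efficacious if "the proportion of infants who require exchange transfusion under FS-PT is no more than 5% greater than the proportion under CPT". No interval, test or alpha accompanies it.

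Under Data collection and analysis, an interval is specified for the primary objective: "A 95% exact binomial confidence interval for the true difference in efficacy between the FS-PT treated and CPT control groups will be calculated". The decision rule follows: "FS-PT will be deemed non-inferior to CPT if the calculated confidence interval does not extend more than 10% below the equivalence point". Both sentences concern efficacy and the 10% margin. The one-sided alpha of 0.025 in the Sample size section also belongs to that comparison. No passage applies an interval or an error rate to the 5% margin.

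**The concern.** A non-inferiority margin is the largest true excess that would be tolerated. The data must therefore rule out an excess of that size, and a confidence limit does this. A rule that asks only whether the observed difference stays within the margin passes about half of all trials in which the true excess equals the margin, whatever the sample size. It also passes a fair share of trials in which the excess is larger.

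Exchange transfusion is the outcome that shows treatment failure most directly, and the article uses it to argue that FS-PT is still better than no treatment. Ten infants treated per exchange prevented is a benefit of 1/10 = 10 points, so the 5-point margin is meant to preserve half of it. A true 7-point excess would give up 7 of those 10 points, and the stated rule would not reliably detect it.

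**Working it through.** **Inputs.** 308 infants per arm (Sample size); 5-point margin (Aims and hypotheses; Secondary outcome). The article gives no CPT exchange-transfusion rate, so 1%, 2%, 5% and 10% are assumed.

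**The plan's own figure.** For the primary outcome, n per arm = (1.960 + 0.842)² × 2 × 0.80 × 0.20 / 0.10² = 251.2, rounded up to 252, or 504 in total. Then 504/0.9 = 560 and 560 × 1.1 = 616. All match the article. No calculation is given for exchange transfusion.

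**The literal rule.** 0.05 × 308 = 15.4, so FS-PT passes if it has at most 15 more infants exchanged than CPT. To a normal approximation,

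P(pass) = Φ((0.05 − δ)/SE), with SE² = [p_F(1 − p_F) + p_C(1 − p_C)]/308 and p_F = p_C + δ.

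- At δ = 0.05 the argument is zero, so P(pass) = 0.50 for any p_C.
- At δ = 0.07 and p_C = 0.05: SE = √[(0.12 × 0.88 + 0.05 × 0.95)/308] = 0.0223, and Φ(−0.02/0.0223) ≈ 0.185.

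**Exact results.** These come from enumerating two independent binomials with 308 per arm. Each cell gives the literal rule / the rule that the upper limit of the two-sided 95% Newcombe interval is below 5 points.

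| Assumed CPT rate | True excess 5 points | 6 points | 7 points | Arms equal |
|---|---|---|---|---|
| 1% | 0.518 / 0.023 | 0.272 / 0.004 | 0.114 / 0.0007 | 1.000 / 0.998 |
| 2% | 0.514 / 0.024 | 0.292 / 0.006 | 0.138 / 0.0011 | 1.000 / 0.977 |
| 5% | 0.508 / 0.025 | 0.329 / 0.008 | 0.189 / 0.0022 | 0.998 / 0.787 |
| 10% | 0.506 / 0.025 | 0.360 / 0.010 | 0.236 / 0.0035 | 0.981 / 0.535 |

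**One possible trial.** Suppose 30/308 infants are exchanged under FS-PT and 15/308 under CPT. The difference is 15/308 = 4.9 points, so the literal rule passes. The Wilson upper limit for 30/308 (0.0974) is 0.1356, and the Wilson lower limit for 15/308 (0.0487) is 0.0297. The Newcombe upper limit is 0.0487 + √[(0.1356 − 0.0974)² + (0.0487 − 0.0297)²] ≈ 0.091. The data would be compatible with an excess of 9 points, close to the whole 10-point benefit.

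**Size needed under an interval rule.** With equal arms, 80% power and one-sided 0.025, n per arm = 7.849 × 2p(1 − p)/0.05², which gives 124, 299 and 566 at p = 2%, 5% and 10%. The planned 308 is about enough at 5% and too few at 10%.

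**The case against.** The strongest reply is that this is simply how the article words a margin. The Evaluation criteria for the primary outcome are equally loose, asking only that average efficacy be "no worse than 10% less than the average efficacy on days where CPT was used", and the analysis section then supplies an interval. The 5% is called a non-inferiority margin, so an interval may be intended here too, and an analysis plan that is not shown may say so. This lowers the severity. It does not remove the point: the article states a success criterion, and the sentence that repairs the primary rule has no counterpart for the 5% margin. Nor does the primary sentence carry over unchanged, since it looks below the equivalence point, whereas here a higher proportion is worse.

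A reader might infer more than the text supports:

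- **Exchanges after exit go uncounted.** The article says "Infants who have been withdrawn from the study will have a physical examination and a final TcB" and gives no counting window. But it defines exit as ceasing to receive phototherapy and nowhere says that later exchanges are excluded. An infant who exits on reaching exchange level is visible through the exit reason.
- **Exits fall mainly on FS-PT and hide part of the margin.** The Sample size section assumes 90% safety in both arms, and the observational study reports that no infant met exclusion criteria. Any figure for hidden events would need an invented exchange rate applied to one arm only.
- **The denominator includes unrandomised infants.** The outcome is "the proportion of enrolled infants who require exchange transfusion", and stage 1 infants are also called enrolled. But the comparison is between proportions under FS-PT and under CPT, and an unrandomised infant belongs to neither.

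**Conclusion.** The point holds for the decision rule alone. The article states a non-inferiority aim with a 5-point margin and gives a rule for it that does not control the error of accepting an unacceptable excess. With 308 per arm and assumed CPT rates of 1% to 10%, the rule as written passes a true 5-point excess about 51% of the time and a true 7-point excess 11% to 24% of the time. An upper 95% Newcombe limit would allow about 2.5% and under 0.5%. The result at 5 points hardly depends on the assumed rate; the results at 7 points and the power figures do.

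Severity is moderate. The outcome is secondary, the primary conclusion has its own interval rule and is unaffected, and the sponsor may already intend an interval.

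**What to change.** In the Secondary outcome section, or beside the primary rule under Data collection and analysis, state that non-inferiority on exchange transfusion requires the upper limit of the two-sided 95% confidence interval (Newcombe or score) for FS-PT minus CPT, by assigned arm among all randomised infants, to lie below 5 points.

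This is a change of wording and needs no extra infants. Its cost is that the claim can fail even when the arms are equal: at 308 per arm, power is about 98%, 79% and 54% at assumed CPT rates of 2%, 5% and 10%. If the expected rate is towards 10%, the plan should acknowledge that the trial may not be able to settle this outcome.

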### Sample size

The minimum sample size was estimated using the following assumptions: 1) the average efficacy of CPT is 80%; 2) the average efficacy of FS-PT is 80%; 3) there will be the same number of infants assigned to both groups; 4) the delta value is 10% - that is, we want to demonstrate that FS-PT is no more than 10% worse than CPT; and 5) 80% power, one-sided alpha = 0.025.

Under these assumptions, a total of 504 days, or 252 days in each treatment group, will be required. This calculation gives the required number of treatment days that are evaluable for efficacy. Since efficacy will be evaluated only for days in which the treatment was deemed safe, the sample size was increased to account for the possibility that the proportion of safe days might be as low as 90%. Assuming that the safety of both FS-PT and CPT is 90%, a sample size of 560 total days is required. Assuming that a typical course of treatment lasts 1 day, both for FS-PT and CPT, then 560 infants, or 280 infants in each group, will be required. Anticipating up to 10% loss due to rainy days (in the FS-PT group), delisting of infants by parents or guardians, or missing data (in both groups), we will enroll 616 infants, or 308 infants in each group. From our year 1 data in the preceding observational study only 66% of the 826 infants referred for elevated TcB had significant elevated TSB levels, hence 915 infants or more will be enrolled for stage 1 bilirubin estimation until the total requirement of 560 treatment days is reached (Figure 
2).

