**Methods/design:**

This prospective, non-blinded randomized controlled non-inferiority trial seeks to enroll infants with elevated total serum/plasma bilirubin (TSB, defined as 3 mg/dl below the level recommended by the American Academy of Pediatrics for high-risk infants requiring PT) who will be randomly and equally assigned to receive FS-PT or CPT for a total of 616 days at an inner-city maternity hospital in Lagos, Nigeria. Two FS-PT canopies with pre-tested films will be used. One canopy with a film that transmits roughly 33% blue light (wavelength range: 400 to 520 nm) will be used during sunny periods of a day. Another canopy with a film that transmits about 79% blue light will be used during overcast periods of the day. The infants will be moved from one canopy to the other as needed during the day with the goal of keeping the blue light irradiance level above 8 μW/cm^2^/nm.

Primary outcome*:* FS-PT will be as efficacious as CPT in reducing the rate of rise in bilirubin levels. Secondary outcome: The number of infants requiring exchange transfusion under FS-PT will not be more than those under CPT.

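### The sample-size chain mixes two inflation rules, 915 does not follow from 616, and the recruitment end-point is given in conflicting units; the power effect is small unless losses fall inside the 560 days

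*Protocol article*

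**What the plan says.** The Sample size section assumes 80% efficacy in each arm, equal allocation, a margin of 10 percentage points and "80% power, one-sided alpha = 0.025". It derives 504 evaluable days (252 per group). It raises this to 560 because as few as 90% of days may be safe, and converts days to infants at one day per infant. For up to 10% further loss from rain, delisting and missing data it concludes: "we will enroll 616 infants, or 308 infants in each group".

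For stage 1 it takes a 66% yield from the preceding observational study and continues: "hence 915 infants or more will be enrolled for stage 1 bilirubin estimation until the total requirement of 560 treatment days is reached".

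The abstract (Methods/design) describes infants "randomly and equally assigned to receive FS-PT or CPT for a total of 616 days".

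The Data collection and analysis section prescribes a 95% exact binomial interval for the difference in efficacy, without naming its construction.

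**The concern.** Two successive 10% allowances are handled by different rules, so the enrolment figure does not restore the 504 days that the section says are required. The stage 1 number is presented as a consequence of what precedes it, but it is not one.

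The quantity that ends recruitment also appears as 616 days, 616 infants and 560 treatment days. Days and infants are interchangeable only while each infant contributes exactly one day. The analysis section itself allows for infants with several treatment days. If courses averaged 1.2 days (an assumption, for illustration), 560 days would be reached at 560/1.2 = 467 infants, so a stop counted in days and a stop counted in infants would be different rules.

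At stake are the moment at which staff stop recruiting and the power that the trial can claim.

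**Working it through.** **Inputs (Sample size section).** Efficacy p = 0.80 in both arms; margin 0.10; one-sided alpha 0.025; power 0.80; safe-day proportion 0.90; further loss up to 0.10; one day per infant; stage 1 yield 0.66.

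**1. Evaluable days.** n per arm = 2p(1−p)(1.960 + 0.842)²/0.10² = 251.2, so 252 per arm and 504 in total. The plan's figure is reproduced by the normal approximation. Power = Φ(0.10/√(0.32/n) − 1.960), which is 80.1% at n = 252.

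**2. Unsafe days.** 504/0.90 = 560. Reproduced.

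**3. Further loss.** The plan's figure is 560 × 1.10 = 616. The rule used in step 2 gives 560/0.90 = 622.2, so 623, or 624 (312 per arm) with equal arms.

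**4. What 616 delivers at the full assumed losses.** 616 × 0.90 = 554 days; × 0.90 = 499 evaluable days, or 249.5 per arm. Power is 79.7%. By comparison, 624 × 0.81 = 505.

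**5. Stage 1.** 616/0.66 = 933.3, so 934. In the other direction, 915 × 0.66 = 604, which is 12 short of 616. If 624 is used, 624/0.66 = 945.5, so 946. The figures 616 with 934 and 624 with 946 are separate chains and should not be mixed.

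**6. What stopping at 560 treatment days delivers.** Let f be the share of the 10% loss that falls inside the 560 counted days. Evaluable days = 560 × (1 − 0.10f) × 0.90.

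| Reading | f | Evaluable days | Power |
|---|---|---|---|
| 560 days counted after losses | 0 | 504 | 80.1% |
| 560 days counted before all losses | 1 | 454 | 75.9% |

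The document does not fix f. A day with a missing bilirubin value could still be counted as a treatment day. So could a partly rainy day on which the infant spent some time under the canopy.

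**7. Power under the planned interval (secondary).** Full enumeration at 252 per arm, 80% efficacy in each arm and a margin of 0.10:

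| Interval for the difference | Power |
|---|---|
| Simple normal (Wald) | 80.2% |
| Asymptotic score (Miettinen-Nurminen) | 79.9% |
| Exact, ordered on the score statistic | 78.9% |
| Exact, ordered on the raw difference | 61.0% |

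**The case against.** The strongest reply is that almost nothing is lost. The core figures, 504 and 560, reproduce exactly. Enrolling 616 absorbs a loss of 56/616 = 9.1% against an allowance worded as an upper limit, and the cost is 5 days and 0.4 points of power. The 915 is a minimum, so it cannot end recruitment early; even treated as a cap it would give 604 × 0.81 = 489 evaluable days and 78.9% power. Within the Sample size section, 560 can be read as the requirement and 616 as that requirement plus an allowance. At one day per infant, the abstract's 616 days is the same number in another unit. The construction of an exact interval is commonly left to an analysis plan, which is not shown here.

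Most of this stands. A reader might infer from the faulty inflation that the trial cannot deliver its 504 days and 80% power; the documents do not support that. If the 560 days are net of losses, recruiting until they are reached gives exactly 504 evaluable days at 90% safe days. Nor is 75.9% the expected power. It requires all of the assumed loss to fall inside the 560 days, whereas the section adds its loss allowance on top of them. The 61% belongs to one construction that the protocol does not choose.

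The reply does not remove the inconsistent inflation or the wrong stage 1 derivation. It also leaves open a stopping count that the text does not define as before or after losses, and an abstract that gives as a total of days what the body uses as a number of infants.

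**Conclusion.** The point holds as an error of arithmetic and of definition, not as a material loss of power.

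- **Inflation:** 616 should be 623, or 624 with equal arms. At the plan's own losses, 616 gives about 499 evaluable days and 79.7% power.
- **Stage 1:** 915 should be 934 if 616 is kept. It is a floor, so the consequence is for planning only.
- **End-point:** the abstract and the Sample size section must be reconciled. Until the 560 days are defined as net or gross of losses, evaluable days range from 454 to 504 and power from 75.9% to 80.1%. This is the part with practical weight, because the count governs when recruitment ends and the Trial status section reports recruitment as ongoing.
- **Interval:** secondary. A score-based method keeps power at 78.9% to 79.9%; an exact interval ordered on the raw difference would give about 61%.

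These figures assume 80% efficacy in both arms, independent days, one day per infant, 90% safe days and the full 10% loss shared equally between the arms.

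**What to change.** 1. State one recruitment end-point, its unit, and that it is net of losses. For example: continue until 560 treatment days with usable start-of-day and end-of-day TSB have accrued, after rain, delisting and missing data, so that 504 are evaluable at 90% safe days. Do not replace the day count with a fixed stop at 616 infants, which yields only about 499.
2. Give the expected enrolment from one chain: either 624 infants (312 per arm) with about 946 at stage 1, or 616 infants with 934 at stage 1 and a restated yield of about 499 evaluable days and 79.7% power.
3. Correct the total of 616 days in the abstract to match.
4. In Data collection and analysis, or in the analysis plan, name the interval as score-based so that it agrees with the sample-size calculation.

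The cost is text only for items 1, 3 and 4, although counting the 560 days net of losses may lengthen recruitment. Adopting 624 adds 8 infants to the 616 and 31 to the 915 at stage 1. Keeping 616 means stating a power slightly below 80%.

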**Figure 2 F2:**
[figure not shown]
**Enrolment flow chart.** CPT, conventional phototherapy; FS-PT, filtered sunlight phototherapy; TcB, transcutaneous bilirubin; TSB, total serum/plasma bilirubin.

